### Randomisation, allocation, and blinding

Eligible patients will be randomly assigned to one of two groups at an allocation ratio of 1:1. The randomisation sequence and grouping will be generated and stored by one researcher who will not be involved directly in participant screening, enrolment, or assessment, using SPSS 20.0 software (IBM Co., Armonk, NY, USA). All random numbers will be listed sequentially, and a set of 10 numbers will be arranged as a cluster (the first 5 for the test group and the last 5 for the control group). Then, random numbers and grouping are inserted in opaque and sealed envelopes sequentially. After all the envelopes have been sealed, they will be distributed to each research centre. Only dentists can open the envelope to check the group allocation and perform the interventions according to the instructions of this study. As a double-blind trial, the patients and outcome evaluators will be blinded to the group assignment until the completion of the study. As dentists cannot be blinded to treatment allocation due to the notable differences in the treatment methods, they will not be allowed to discuss the type of intervention with either patients or outcome evaluators.

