#### First Appointment

With the aim of infection control and inflammation relief, the first appointment will be the same for all patients in this study. The first appointment will include the following components:
*Anaesthesia and isolation*. After local anaesthesia with articaine hydrochloride and epinephrine tartrate injection (with 1:100,000 adrenaline [Produits Dentaires Pierre Rolland, Merignac, France]), the tooth is isolated with a rubber dam and disinfected.*Access preparation*. All decayed areas of the tooth will be removed, and the pulp chamber will be completely unroofed.*Root canal preparation*. The working length and the initial apical file will be determined.*Root canal irrigation*. As canal disinfection relies considerably on chemical irrigants, the needle will be placed with the side-port vents into the apical third of the tooth and irrigation will be accomplished using needles with a slow infusion rate. The canal will be copiously irrigated in three steps using ultrasonic irrigation with interspersed drying with sterile paper points. A 5-min irrigation with 20 mL 1.0% sodium hypochlorite (NaClO) (Longly biomedical, Wuhan, China) will be followed by a simple irrigation with 5-mL sterile saline solution (Baxter Healthcare, Shanghai, China), ending with a 5-min irrigation with 20 mL 17% ethylene diamine tetraacetie acid (EDTA) (Longly biomedical, Wuhan, China).*Medicated intra-pulpal dressings*. To restrict bacterial regrowth and supply continued disinfection, the root canal will be filled homogeneously to the working length with calcium hydroxide paste (CALXYL X-Ray Visible, OCO Praparate GmBh, Dirmstein/Pfalz, Germany) [45]. Then, glass ionomer (GC Fuji IX, GC Corporation, Tokyo, Japan) will be placed onto the intracanal dressing.

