#### Second Appointment

After 2–4 weeks, patients will return for a second visit. If the symptoms are not relieved, the root canals will be re-treated with calcium hydroxide. Patients with no symptoms will proceed to the next RET treatment steps (Fig. 3).
Cleaning, anaesthesia, field isolation, disinfection of the operating field, and temporary seal removal*Root canal irrigation*. The canal will be irrigated with 20 mL of 17% EDTA for 5 min to flush out the calcium hydroxide paste, followed by irrigation with sterile saline solution to decrease the cytotoxicity of EDTA. After drying the canal using sterile paper points, the two groups of patients will experience different revascularization procedures.*PRF preparation*. To prepare PRF, 10 mL of whole blood from the median cubital vein will be drawn into 10-ml plastic tubes (Kangjian Medical, Jiangsu, China) without anticoagulant reagent and centrifuged at 800 rpm for 3 min with Centrifuge (Process for PRF, FRANC). After centrifugation, the upper yellow fluid liquid (i-PRF) will be collected as close as possible to the layer of red cells (Fig. 4).*RET with i-PRF (the test group)*. K-files will be intentionally used to violate the periapical tissues via overinstrumentation up to 2–3 mm beyond the apical foramen to provoke bleeding. However, only the apex third of the root canal will be filled with blood. The i-PRF will be injected into the root canal to a level 3 mm below the cementoenamel junction (CEJ). After a 10–15-min period for coagulation, the PRF will be covered by a 3-mm layer of iRoot BP Plus (Innovative Bioceramix Inc., Vancouver, Canada).*RET with BC (the control group)*. K-files will be intentionally used to violate the periapical tissues via overinstrumentation up to 2–3 mm beyond the apical foramen to provoke bleeding. The blood will be permitted to fill the canal space to a level 3 mm below the CEJ. After a 10–15-min period for coagulation, the BC will be covered by a 3-mm layer of iRoot BP Plus.*Cavity restoration*. A layer of self-adhering flowable composite (Kerr Dyad Flow, Kerr, CA, USA) will be applied on top of the iRoot BP Plus layer as a cavity liner, and the final filling will be accomplished with resin with adhesive for permanent restoration.

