### Outcome measures

Variables will be measured at baseline and at 1, 3, 6, 12, 18, and 24 months after the treatment. At each appointment, a clinical examination, a periapical radiograph, and pulp tests (thermal and electric) will be performed. CBCT images will be obtained at baseline and 24 months after the treatment to evaluate the apical shadow. The primary outcome of this study is the success rate of RET 24 months postoperatively, which will be obtained by evaluating the clinical and radiographic outcomes. The secondary outcomes include the subjective response from the patient to thermal and electric stimuli, which reflects the responsiveness of regenerative pulpal sensory neurons. Safety will be evaluated via the analysis of the presence of adverse events during the study. The evaluators will complete standardised training prior to the study period. Two trained dentists will independently evaluate and disagreements will be resolved through a discussion with a third evaluator.

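### As written, the patient blind is not secured: an arm-vein draw to make i-PRF is described at the second visit, with no matching draw or masking stated for controls

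*Protocol article*

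**What the plan says.** Under Randomisation, allocation, and blinding, the protocol article states that "the patients and outcome evaluators will be blinded to the group assignment until the completion of the study". Operators are excepted, because "dentists cannot be blinded to treatment allocation due to the notable differences in the treatment methods". The one safeguard given for the patient blind is that the dentists know the allocation but "they will not be allowed to discuss the type of intervention with either patients or outcome evaluators".

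Under First Appointment, "the first appointment will be the same for all patients in this study". No such statement is made for the second visit. Under Second Appointment, once the canal has been dried, "the two groups of patients will experience different revascularization procedures". The next listed step reads: "To prepare PRF, 10 mL of whole blood from the median cubital vein will be drawn into 10-ml plastic tubes". Two further steps follow, one labelled for the test group, in which i-PRF is injected into the canal, and one labelled for the control group, in which the canal fills with bleeding provoked at the apex. The caption to Fig. 3 also assigns i-PRF to the test group alone.

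On endpoints, Outcome measures says: "The secondary outcomes include the subjective response from the patient to thermal and electric stimuli". Primary outcome measures requires, for success, a symptom-free tooth without pain on percussion or tenderness, together with several observed signs and a radiographic criterion.

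**The concern.** A patient blind holds only if what the patient experiences is the same in both arms or is disguised. A needle in the arm is an obvious event, the only anaesthesia the article describes is local, and a dentist's silence does not conceal it. If only test patients are bled, anyone who knows that the new product is made from their own venous blood can work out their group.

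This matters because patient reports enter both efficacy endpoints. Under Secondary outcome measures, the thermal test grades what the patient feels against a control tooth, and the electric reading is taken when the patient signals a response. Neither test has a component independent of the patient. In the primary outcome, the absence of symptoms, percussion pain and tenderness likewise depends on report. Expectation in favour of the novel scaffold could make i-PRF look better on these items without any true difference.

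**Working it through.** **Step 1: the text, side by side.**

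| Question | What the article states | Where |
|---|---|---|
| Are patients blinded? | Yes, to study end | Randomisation, allocation, and blinding |
| By what means? | Dentists do not discuss the intervention | Same section |
| Is the first visit the same in both arms? | Yes | First Appointment |
| Is the second visit the same? | No; procedures differ | Second Appointment |
| Is there a venous draw? | 10 mL, to prepare PRF; step carries no group label | Second Appointment |
| Who receives i-PRF? | Test group only | Second Appointment; Fig. 3 caption |
| Do controls have a draw, sham or masking? | Not stated | – |

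The draw's stated purpose is a product that only the test group receives, and it follows the sentence announcing different procedures. The natural reading is a draw in the test group only, which conflicts with the blinding claim.

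**Step 2: how much could it matter?** The Sample size section gives 346 patients (173 per group), α = 0.05 and 80% power. It gives no success rates, so that figure cannot be reproduced. This point does not depend on it.

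The documents give no size for a reporting bias, so what follows is an illustration. Assumptions: no true effect, a two-sided test (sidedness is not stated), all 173 per arm analysed, true success p = 0.80 in both arms, and a reporting shift b that adds to apparent success in the test arm only.

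With p₂ = p + b and p̄ = (p + p₂)/2:

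- SE₀ = √[2p̄(1 − p̄)/173]
- SE₁ = √{[p(1 − p) + p₂(1 − p₂)]/173}
- Rejection rate = Φ[(b − 1.96·SE₀)/SE₁] + Φ[(−b − 1.96·SE₀)/SE₁]

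For b = 0.05:

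- p̄ = 0.825
- SE₀ = √(0.28875/173) = 0.0409
- SE₁ = √(0.2875/173) = 0.0408
- First term: Φ[(0.05 − 0.0801)/0.0408] = Φ(−0.74) = 0.230
- Second term: about 0.001
- Total: 0.231

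| Shift b | Teeth per arm (173·b) | Share of non-successes reversed (b/0.20) | False-positive rate at p = 80% | Range for p = 70% to 90% |
|---|---|---|---|---|
| 2 points | 3.5 | 10% | 7.6% | 6.9–9.9% |
| 5 points | 8.7 | 25% | 23% | 18–42% |
| 8 points | 13.8 | 40% | 53% | 40–88% |

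No comparable illustration is offered for the pulp tests, because the article gives no expected response rates.

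**The case against.** The strongest reply is that the PRF preparation step has no group label, while the two steps after it do. An article that labels its arm-specific steps but leaves this one unlabelled may mean that everyone is bled and only the use of the blood differs. A journal article may also leave masking details to the full protocol. Whether the draw reveals the arm depends on what patients are told, and the consent text is not shown.

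This limits how far the point can go. A reader might infer that the trial is not double-blind, or that all 346 patients will know their arm. The documents support neither: they do not expressly withhold the draw from controls, and they do not show what patients know about its purpose. It does not dispose of the point. The article sets out both procedures step by step and affirmatively claims patient blinding, and the steps as described do not deliver it. That is more than an omitted detail.

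A second reply is that much of the primary outcome cannot respond to expectation: percussion sound, loosening, swelling, sinus or fistula, and the apical shadow. Two trained evaluators assess independently, with a third for disagreements. Only a tooth that would fail solely on a patient-reported item can move, so the 8-point shift, which reverses 40% of non-successes, is demanding. This is fair, and it is why no single figure should be read as the expected bias. A reader might also infer that the evaluator blind falls. A patient could mention the draw to an evaluator, but nothing in the draw itself discloses the arm to evaluators.

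**Conclusion.** The point stands in a limited form. The blinding section claims a property for patients that the second-appointment procedure, followed as written, does not secure. The exposure is confined to the thermal and electric pulp tests, which rest wholly on patient response, and to the symptom items of the primary outcome.

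The size of any bias cannot be derived from the documents. The illustrative false-positive rates run from modest (about 7.6% for a 2-point shift at 80% success) to severe (about 53% for 8 points). They rest on an assumed success rate, an assumed shift wholly in favour of i-PRF, no true effect and complete data. They show that a small shift in reports could matter at this sample size, not that it will occur. If the same draw is in fact done in every patient, one sentence saying so would resolve this conflict.

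**What to change.** 1. Reconcile Randomisation, allocation, and blinding with Second Appointment by stating whether controls also have the venous draw or, if not, how the difference is masked from patients.
2. If neither applies, replace double-blind with evaluator-blinded in the Abstract (Methods), the closing paragraph of Background, Study design and objectives, and the blinding section. The title does not use the term and needs no change.
3. Ask all patients, in neutral terms, not to discuss any aspect of their treatment with evaluators. The request should not name the blood draw, since that would point to it as the marker of allocation.
4. In that same case, pre-specify a supporting analysis of the 24-month primary outcome using only evaluator-observed signs and the radiographic reading, shown beside the main result. It answers a narrower question, because it sets real symptoms aside, so it supports the main analysis and does not replace it.
5. Report the pulp-test comparisons as open to patient expectation.

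The cost is some rewording, one extra table and, if the patient blind cannot be supported, loss of the double-blind label. Recruitment was under way at publication, and the article requires amendments to be approved by the ethics committee and the funding support departments, so the change should be made promptly and before any outcome data are compared by group.

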### Interventions

According to the latest RET operating guidelines issued by the American Academy of Endodontics (AAE) [43] and the European Society of Endodontics (ESE) [44], the standardised operating procedure of RET requires two treatment visits. During the first appointment, infection is controlled and inflammation is relieved. Pulp regeneration and revascularization is accomplished during the second appointment. All RET procedures will be performed under a dental microscope, except anaesthesia and rubber dam placement steps.

#### First Appointment

With the aim of infection control and inflammation relief, the first appointment will be the same for all patients in this study. The first appointment will include the following components:
*Anaesthesia and isolation*. After local anaesthesia with articaine hydrochloride and epinephrine tartrate injection (with 1:100,000 adrenaline [Produits Dentaires Pierre Rolland, Merignac, France]), the tooth is isolated with a rubber dam and disinfected.*Access preparation*. All decayed areas of the tooth will be removed, and the pulp chamber will be completely unroofed.*Root canal preparation*. The working length and the initial apical file will be determined.*Root canal irrigation*. As canal disinfection relies considerably on chemical irrigants, the needle will be placed with the side-port vents into the apical third of the tooth and irrigation will be accomplished using needles with a slow infusion rate. The canal will be copiously irrigated in three steps using ultrasonic irrigation with interspersed drying with sterile paper points. A 5-min irrigation with 20 mL 1.0% sodium hypochlorite (NaClO) (Longly biomedical, Wuhan, China) will be followed by a simple irrigation with 5-mL sterile saline solution (Baxter Healthcare, Shanghai, China), ending with a 5-min irrigation with 20 mL 17% ethylene diamine tetraacetie acid (EDTA) (Longly biomedical, Wuhan, China).*Medicated intra-pulpal dressings*. To restrict bacterial regrowth and supply continued disinfection, the root canal will be filled homogeneously to the working length with calcium hydroxide paste (CALXYL X-Ray Visible, OCO Praparate GmBh, Dirmstein/Pfalz, Germany) [45]. Then, glass ionomer (GC Fuji IX, GC Corporation, Tokyo, Japan) will be placed onto the intracanal dressing.

#### Second Appointment

After 2–4 weeks, patients will return for a second visit. If the symptoms are not relieved, the root canals will be re-treated with calcium hydroxide. Patients with no symptoms will proceed to the next RET treatment steps (Fig. 3).
Cleaning, anaesthesia, field isolation, disinfection of the operating field, and temporary seal removal*Root canal irrigation*. The canal will be irrigated with 20 mL of 17% EDTA for 5 min to flush out the calcium hydroxide paste, followed by irrigation with sterile saline solution to decrease the cytotoxicity of EDTA. After drying the canal using sterile paper points, the two groups of patients will experience different revascularization procedures.*PRF preparation*. To prepare PRF, 10 mL of whole blood from the median cubital vein will be drawn into 10-ml plastic tubes (Kangjian Medical, Jiangsu, China) without anticoagulant reagent and centrifuged at 800 rpm for 3 min with Centrifuge (Process for PRF, FRANC). After centrifugation, the upper yellow fluid liquid (i-PRF) will be collected as close as possible to the layer of red cells (Fig. 4).*RET with i-PRF (the test group)*. K-files will be intentionally used to violate the periapical tissues via overinstrumentation up to 2–3 mm beyond the apical foramen to provoke bleeding. However, only the apex third of the root canal will be filled with blood. The i-PRF will be injected into the root canal to a level 3 mm below the cementoenamel junction (CEJ). After a 10–15-min period for coagulation, the PRF will be covered by a 3-mm layer of iRoot BP Plus (Innovative Bioceramix Inc., Vancouver, Canada).*RET with BC (the control group)*. K-files will be intentionally used to violate the periapical tissues via overinstrumentation up to 2–3 mm beyond the apical foramen to provoke bleeding. The blood will be permitted to fill the canal space to a level 3 mm below the CEJ. After a 10–15-min period for coagulation, the BC will be covered by a 3-mm layer of iRoot BP Plus.*Cavity restoration*. A layer of self-adhering flowable composite (Kerr Dyad Flow, Kerr, CA, USA) will be applied on top of the iRoot BP Plus layer as a cavity liner, and the final filling will be accomplished with resin with adhesive for permanent restoration.

**Fig. 3 Fig3:**
[figure not shown]
Regenerative endodontics therapy procedures. The steps of regenerative endodontics therapy (RET) with injectable platelet-rich fibrin (i-PRF) and with blood clot are shown. **A** After 2–4 weeks of intercanal medication, **B** the temporary seal is removed. **C** The root canal is irrigated and **D** dried with sterile paper points. **E** Bleeding is provoked. **F** i-PRF and cavity restoration are performed in the test group. **G** Blood clot and cavity restoration are performed in the control group

**Fig. 4 Fig4:**
[figure not shown]
The preparation of injectable platelet-rich fibrin. After centrifugation (800 rpm, 3 min), injectable platelet-rich fibrin (i-PRF) is collected from the upper yellow fluid liquid

### Outcome measures

Variables will be measured at baseline and at 1, 3, 6, 12, 18, and 24 months after the treatment. At each appointment, a clinical examination, a periapical radiograph, and pulp tests (thermal and electric) will be performed. CBCT images will be obtained at baseline and 24 months after the treatment to evaluate the apical shadow. The primary outcome of this study is the success rate of RET 24 months postoperatively, which will be obtained by evaluating the clinical and radiographic outcomes. The secondary outcomes include the subjective response from the patient to thermal and electric stimuli, which reflects the responsiveness of regenerative pulpal sensory neurons. Safety will be evaluated via the analysis of the presence of adverse events during the study. The evaluators will complete standardised training prior to the study period. Two trained dentists will independently evaluate and disagreements will be resolved through a discussion with a third evaluator.

#### Primary outcome measures

The therapeutic effect evaluation criteria are the following:
*Success*. After RET, the tooth is asymptomatic, with an absence of percussion pain, bone adhesion percussion sound, loosening, tenderness, mucosal swelling, sinus, or fistula. The radiographic examination demonstrates the absence of an apical shadow or a reduced apical shadow.*Failure*. After RET, the tooth is symptomatic, with symptoms of apical infection such as pain and fistula. The radiographic examination demonstrates a new-onset apical shadow or an enlarged apical shadow.

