#### Statistical analysis

The data will be analysed by an independent statistician using SPSS 20.0 software (IBM Co., Armonk, NY, USA) at the end of the study to evaluate the evolution. The continuous variables will be described as the mean (standard deviation) or median and analysed using parametric methods. Categorical variables will be described as percentages and analysed using non-parametric methods. The level of significance will be *P* < 0.05, and 95% confidence intervals will be calculated.
*Baseline analysis*

The two groups will be comparable in terms of sex, age, tooth position, disease type, and apical hole size. Quantitative variables will be analysed using a one-way analysis of variance (independent sample t-test) or non-parametric methods if the data do not meet and cannot be transformed to meet parametric assumptions. Qualitative variables will be analysed using the Wilcoxon rank-sum test. A principal component analysis will be performed using multinomial logistic regression to adjust for potential confounders.
(2)*Main outcome analysis*

The inter-group comparison of success rates will be analysed using the chi-square test. If there are baseline variables influencing the comparability of the two groups, a logistic regression model will be used to eliminate the effects of these confounders on the success rate and the odds ratio (OR) will be calculated. For the missing data, the last observation carry forward method will be adopted to fill the validity analysis, that is, the case data that fails to observe the whole treatment process will be transferred to the final result of the test with the last observation data.
(3)*Secondary outcome analysis*

For intra-group comparisons, McNemar’s test will be used to analyse the clinical outcomes of different centres. For inter-group comparisons, the secondary outcome will be analysed using the Chi-square test.
(4)*Safety evaluation analysis*

The adverse events that occur during the study period will be listed for each group and compared using the chi-square test. The security evaluation does not evaluate missing data.

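### Baseline lesion status is built into the success definition, yet the primary comparison ignores it unless an observed imbalance triggers adjustment, and the pooled success rate depends on case mix

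*Protocol article*

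**What the plan says.** All references are to the protocol article.

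- **Inclusion criteria.** Necrotic mature teeth are eligible with a periapical lesion or without one. No limit is set on either kind.
- **Primary outcome measures, Success.** The clinical part applies to every tooth: "After RET, the tooth is asymptomatic, with an absence of percussion pain, bone adhesion percussion sound, loosening, tenderness, mucosal swelling, sinus, or fistula". The radiographic part is: "The radiographic examination demonstrates the absence of an apical shadow or a reduced apical shadow".
- **Primary outcome measures, Failure.** The radiographic part is: "The radiographic examination demonstrates a new-onset apical shadow or an enlarged apical shadow".
- **Outcome measures.** "CBCT images will be obtained at baseline and 24 months after the treatment to evaluate the apical shadow". CBCT is also used to confirm eligibility, so lesion status can be read before allocation.
- **Randomisation, allocation, and blinding.** "All random numbers will be listed sequentially, and a set of 10 numbers will be arranged as a cluster", five per group. No stratification factor is named.
- **Statistical analysis.** "The inter-group comparison of success rates will be analysed using the chi-square test". A logistic model giving an odds ratio follows only if baseline variables are found to affect comparability. The listed baseline variables are sex, age, tooth position, an undefined disease type, and apical hole size.
- **Study design and objectives.** The primary objective covers the efficacy of RET itself as well as of RET with i-PRF. Both arms receive RET, and there is no root canal therapy arm.

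**The concern.** One radiographic rule sets two different tasks. No change from baseline is a pass for a lesion-free tooth and not a pass for a tooth with a lesion. The Failure wording divides the same way: a new shadow can arise only where there was none, and an enlarged one only where there was one already. A variable this closely tied to the endpoint's definition is a natural candidate for the primary model.

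Two things are at stake.

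1. **Precision and a fixed analysis.** Variance that lesion status could explain stays in the error term. Whether the result is an unadjusted comparison of rates or an adjusted odds ratio also depends on what the baseline table happens to show.
2. **Meaning of the absolute rate.** With no arm outside RET, the evidence on RET itself is the success rate within the arms. Randomisation does not protect that rate from case mix.

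**Working it through.** **The plan's own figure.** The article gives 346 patients (173 per group) at α = 0.05 and 80% power, without success rates, a difference or a dropout allowance. It can be neither reproduced nor refuted. With a two-sided test and no continuity correction, pairs such as 50 v 65%, 61 v 75%, 69 v 82%, 74 v 86% and 82 v 92% all come within 3% of 173 per group. The point below uses only the 173.

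**Assumed inputs (none are in the article).** Success is 95% without a lesion and b = 65% or 75% with one. The share of teeth with a lesion is w = 30%, 50% or 70%. Each patient contributes one tooth. The rates are applied alike to both arms, to isolate the prognostic effect.

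**Step 1: pooled rate and variance explained by lesion status.**

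Pooled rate: p = (1 − w)(0.95) + w·b.

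Share of variance removed = 1 − [(1 − w)(0.95)(0.05) + w·b(1 − b)] / [p(1 − p)].

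| w | b | p | within-stratum variance | p(1 − p) | share removed |
|---|---|---|---|---|---|
| 0.3 | 0.75 | 0.89 | 0.0895 | 0.0979 | 8.6% |
| 0.3 | 0.65 | 0.86 | 0.1015 | 0.1204 | 15.7% |
| 0.5 | 0.75 | 0.85 | 0.1175 | 0.1275 | 7.8% |
| 0.5 | 0.65 | 0.80 | 0.1375 | 0.1600 | 14.1% |
| 0.7 | 0.75 | 0.81 | 0.1455 | 0.1539 | 5.5% |
| 0.7 | 0.65 | 0.74 | 0.1735 | 0.1924 | 9.8% |

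The range is 5.5% to 15.7%. The standard error of the difference in rates shrinks by 1 − √(1 − 0.055) ≈ 3% to 1 − √(1 − 0.157) ≈ 8%.

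**Step 2: movement of the absolute rate.** As w goes from 0.3 to 0.7 with nothing else changed, p falls from 89% to 81% (8 points, b = 0.75) or from 86% to 74% (12 points, b = 0.65).

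**Step 3: chance imbalance between arms.** The SD of the difference in lesion prevalence is √[2w(1 − w)/173], which is 0.049 at w = 0.3 or 0.7 and 0.054 at w = 0.5. A 2-SD imbalance times the 20–30 point gap in success shifts the observed difference by 2 × 0.049 × 0.20 = 2.0 points up to 2 × 0.054 × 0.30 = 3.2 points. The standard error of the unadjusted difference, √[2p(1 − p)/173], runs from 3.4 points (p = 0.89) to 4.7 points (p = 0.74). In units of that standard error the shift is 2 × √(share removed), at most 2 × √0.157 = 0.79. Even an unusual imbalance therefore moves the result by less than one standard error.

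**Step 4: precision of stratum-specific rates.** Lesion teeth per arm number 173w, about 52 to 121. The 95% half-width for their success rate is 1.96 × √(0.1875/121) ≈ 8 points at best and 1.96 × √(0.2275/52) ≈ 13 points at worst. For the pooled arm rate, 1.96 × √[p(1 − p)/173] is about 5 to 7 points.

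**The case against.** **The comparison is already valid.** With 1:1 randomisation of 346 patients, lesion status is balanced in expectation, and chance imbalance is part of the sampling error that the chi-square test covers. This stands. A reader might infer from the two radiographic bars that the between-arm comparison is biased. The documents do not support that, and Step 3 shows that even a 2-SD imbalance stays under one standard error.

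**The plan already handles it.** Disease type may be meant to capture lesion status, logistic regression is planned, and the secondary aim is to study factors that influence outcome. This stands in part. The term is undefined, the adjustment depends on what the data show, and adjusting only after imbalance gives up the precision available when the arms are balanced.

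**Lesion-free teeth are informative.** A reader might infer that they cannot fail or can show no benefit. That goes too far: the clinical criteria apply to every tooth, and a new shadow counts against success. They cannot show radiographic healing, but they can fail.

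**The numbers are assumed.** This stands. If both kinds of tooth had the same success rate, case mix would not matter. The article gives no rates, so only the direction, and not the size, can be argued from its text.

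**Breadth is a legitimate choice, and reporting by subgroup usually belongs in the SAP.** Both are fair. The point concerns what the article does fix: an unadjusted primary test with a data-dependent trigger. Stratum-specific reporting is a recommendation, not an omission held against the article.

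**Conclusion.** The point holds as a matter of efficiency and interpretation. The success definition makes baseline lesion status a likely strong predictor, while the stated primary test uses it only if imbalance is noticed. Under the assumed rates the cost is about 5–16% of outcome variance (3–8% of the standard error), and case mix alone moves the pooled success rate by 8–12 points.

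Two stronger conclusions are tempting and are not supported.

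- **That the trial is underpowered because lesion-free teeth dilute the effect.** This needs an assumed smaller effect in those teeth. Nothing shows that the 346 was not planned on mixed-population rates.
- **That stratifying would remove the dependence on case mix.** It would not. If i-PRF added 12 points in lesion teeth and 2 in lesion-free teeth (assumed), the average effect would be 12w + 2(1 − w) = 5, 7 or 9 points at w = 30%, 50% or 70%. A Mantel-Haenszel difference would average the strata in much the same way. Only separate reporting answers that part.

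A lesion of unchanged size meets neither the Success nor the Failure radiographic wording. That is a separate gap, and this point does not rest on it, but its coding will affect the rate in lesion teeth.

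**What to change.** 1. **Keep the allocation list.** Recruitment is under way (Trial status), so new envelope series would be awkward, and the analysis can recover the precision without them.
2. **Pre-specify lesion status, present or absent on the baseline CBCT, in the primary comparison regardless of observed imbalance.** One suitable form is a Mantel-Haenszel risk difference with its 95% confidence interval. Logistic regression including lesion status is an alternative. Name one as primary, because the logistic odds ratio is conditional on lesion status and is on a different scale from a difference in rates.
3. **State whether disease type in the baseline list means lesion status.** If it does not, add lesion status to the list.
4. **Report 24-month success by arm separately for the two kinds of tooth**, with confidence intervals, so that healing of existing lesions can be told apart from absence of new disease.

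The cost is a few lines of analysis text. CBCT is already taken at baseline, so no new data are needed. The stratum-specific rates will be less precise than the pooled ones: about ±8 to ±13 points for lesion teeth, against ±5 to ±7 points for a whole arm, under the assumptions above. They should be read as descriptive.
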